### Assessments

Assessments were conducted by trained RAs as outlined in Table 2. The RAs are blinded to study condition at baseline (i.e., assessments are administered prior to randomization). RAs are not blind to study condition at follow-up visits. All participants are sought for follow-up assessments at 3- and 6-months post-enrollment. Assessments consist of a battery of instruments to measure outcomes including, by not limited to: OUD severity (modified World Mental Health Composite International Diagnostic Interview [CIDI]) [37], substance use (Addiction Severity Index-Lite) [40], health and functioning (World Health Organization Quality of Life [WHOQOL-BREF]) [41], psychological stress (Kessler-6 scale) [42], and treatment utilization data. Urine toxicology is collected at baseline, 3-, and 6-month follow-up interviews and tested for fentanyl, opiates, oxycodone, methadone, buprenorphine, cocaine, cannabis, alcohol, amphetamines, and benzodiazepines. Following the increase of xylazine in the illicit drug supply, an additional dip test for xylazine was included in the urine toxicology panel.

### Primary Outcome

The primary outcome is OUD treatment entry within 30-days post-enrollment, defined as admission to a buprenorphine provider (either office-based care or a specialty OUD program) or alternative OUD treatment modalities (e.g., methadone, medical detox followed by behavioral treatment). OUD treatment entry and retention will be collected by self-report. To the extent possible, treatment data will be verified via provider or treatment records with participants’ written permission. Treatment retention (defined as total number of days in MOUD treatment) will be examined as a secondary outcome. OUD treatment entry within 30-days of study enrollment is the primary outcome because linkage to such treatment is the main and most proximate goal of the service strategies being tested.

To assess for treatment entry and retention, at each follow-up assessment, participants are asked whether they enrolled in treatment for drugs or alcohol since their last assessment. If the participant reports one or more treatment episodes, research staff collect details of each episode including start/end dates, type of setting (e.g., inpatient, outpatient, detox), receipt of medication (e.g., buprenorphine, methadone), and whether they attended self-help groups.

### Statistical Analysis

Outcomes will be examined via a generalized linear modeling framework (for endpoint analyses, such as OUD treatment entry), with extension to generalized linear mixed modeling for repeated measures models (for analyses of differential change, e.g., days of drug use).

#### Outcome variables

Outcome variables will be either: (1) dichotomous variables (e.g., entry into treatment, urine test results), assumed to follow a binomial distribution; or (2) discrete random variables (e.g., days of drug use), assumed to follow a Poisson distribution. All distributional assumptions will be evaluated prior to analyses, and if violated, suitable alternatives will be chosen (e.g., allowing for over-dispersion in Poisson models).

#### Explanatory variables

The explanatory variables in the statistical model will include: (1) *Study Condition* (*PN + BUP vs PN vs Usual Care)* and (2) *Recruitment Site (Clinic Site, Social Network, Other)*. For variables analyzed as repeated measures, the model will also include (3) *Time* and its interaction with *Condition*.

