#### Patient navigation services (PN)

Participants assigned to the PN condition receive the same standard care from their providers described for UC. In addition, PN participants meet with a Patient Navigator immediately following randomization at the baseline visit. During the initial meeting, the Patient Navigator assesses readiness for SUD treatment, barriers to care, and other social determinants of health. The Patient Navigator delivers a motivational intervention as appropriate, develops rapport, and makes a treatment plan with the participant. Using patient navigation and motivational intervention techniques, the Patient Navigator continues to coordinate with participants for up to 2 months to identify available resources and strategies to resolve discussed barriers (e.g., transportation, insurance coverage, governmental assistance). Navigators have a small fund available (typically not exceeding $100 total per participant) to assist patients with needs such as medical co-pays, obtaining ID cards, transportation, low-cost phones/cell phone minutes, and other related items. Table 1 shows examples of common barriers and how the Navigators would address them, as adapted from our team’s previous patient navigation work [15,39].

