The social network referral strategy has singularly improved recruitment efforts compared to the clinic screening. Between May 2023 and July 2023, 79 participants were enrolled—a significant increase in enrollment compared to those in 2021 and 2022. Using this novel recruitment strategy, we may be able to understand if Patient Navigation techniques can not only improve linkages to OUD treatment among sexual health patients, but also facilitate service linkage for those referred by their peers. Notably, this strategy has some parallels with how sexual health clinics already function in another domain, namely through disease intervention specialists that identify and treat partners of individuals with sexually transmitted infections. Evaluating these touchpoints as facilitators to OUD treatment may shed light on how researchers and clinicians can engage individuals with untreated OUD using novel strategies such as social network connection. These techniques may resolve barriers to engagement in research such as institutional distrust [43] by allowing potentially eligible participants to learn about research opportunities through their trusted peers. Furthermore, it is important to examine how social networks may be a viable pathway to encourage and empower individuals with untreated OUD to seek evidence-based treatment services that they otherwise would not pursue independently. Still, there are potential confounders that may be introduced through the use of social network referrals. Social support has been identified as a predictor of treatment entry and engagement, but findings are mixed [44-46]. It is possible that greater social network support may influence readiness for treatment entry. Thus, it will be important to consider the association of social networks, such as familial support, on the primary outcome of treatment entry in this study.

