**Figure 2. F2:**
[figure not shown]
Study and Recruitment Flow.

**Table 1. T1:** Examples of Potential Barriers to Engaging in Care and Navigator Response.

Example of Barrier	Navigator response
Ambivalence for SUD treatment	Use motivational interventions to explore and resolve ambivalence; Deliver basic education to address health beliefs and increase health literacy about treatment options.
Discomfort interacting with treatment staff	Explore underlying reasons for patient discomfort (e.g., low health literacy; perceived stigma) and address with education and/or role playing; Advocate for patient with treatment staff.
Lacks health insurance or has insufficient coverage	Identify appropriate insurance eligibility and options; Help patient fill out application and interface with insurance bureaucracies on patient’s behalf.
Cannot afford recommended medicines	Identify and help patient sign up for prescription assistance programs; Interface with physician(s) to discuss less costly alternatives.
SUD treatment program requires photo ID	Identify nearest DMV; Assist with transportation; Assist with fees.
Recommended care is far or inconvenient	Assist with transportation; Facilitate transfer to closer providers.
Missed appointment	Appointment reminders; Accompany patient to appointment; Reschedule.

Note: This table has been adapted from previously published patient navigation work from our team [39].

**Table 2. T2:** Data collection schedule and measures.

Measures	Baseline	3-month	6-month
Illicit drug use (urine test)	♦	♦	♦
Substance use patterns (ASI-Lite)	♦	♦	♦
OUD diagnostic criteria (Modified CIDI)	♦	♦	♦
HIV risk behavior	♦	♦	♦
Quality of Life (WHOQOL-BREF)	♦	♦	♦
Psychological distress (Kessler-6)	♦	♦	♦
Patient navigation satisfaction		♦	
SUD treatment utilization	♦	♦	♦

**Table 3. T3:** Screening rates by strategy from 2021 through July 2023.

Screening Metric	Single-Item Screening		TAPS Tool In-Person	Network Referrals
	Telehealth	In-Person		
Total records	108	810	4059	136
Completed brief OPI screen	107 (99.1)	802 (99.0)	3874 (95.4)	133 (97.8)
Past 30-day opioid use	11 (10.1)	36 (4.4)	98 (2.4)	128 (94.1)
No past 30-day opioid use	96 (88.9)	766 (94.6)	3776 (93.0)	5 (3.7)
Missing	1 (0.9)	8 (1.0)	185 (4.6)	2 (2.2)
Completed TAPS Tool screen	N/A	N/A	2429 (65.8)	N/A
Missing			1265 (34.2)	

Notes: TAPS Tool = Tobacco, Alcohol, and other Substance use Tool.

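### The outcome model for treatment entry names no patient-level baseline covariate, although suitable ones are already collected; a small, nearly costless gain in precision goes unused

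*Protocol article*

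**What the plan says.** The Primary Outcome section fixes a binary endpoint: "The primary outcome is OUD treatment entry within 30-days post-enrollment". The Statistical Analysis section places it in the general framework: "Outcomes will be examined via a generalized linear modeling framework (for endpoint analyses, such as OUD treatment entry". The Explanatory variables section then says "The explanatory variables in the statistical model will include" the study condition and a second term, "Recruitment Site (Clinic Site, Social Network, Other". Repeated-measures models add time and its interaction with condition. No severity, drug-use or treatment-history variable is named.

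The Assessments section describes one instrument as measuring "OUD severity (modified World Mental Health Composite International Diagnostic Interview [CIDI". In Table 2 the row "OUD diagnostic criteria (Modified CIDI" is marked at baseline, as are the rows for ASI-Lite substance use patterns and SUD treatment utilization. Under Randomization, and Baseline Procedures, baseline assessments are completed before allocation. These three measures are therefore true baseline variables, available in all three arms.

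**The concern.** Severity of OUD, recent opioid use and earlier contact with treatment are plausible predictors of whether someone enters treatment within 30 days. Adjusting for a prognostic baseline variable in a randomized comparison sharpens the treatment contrast without needing another participant. That matters here because the Sample Size and Power section concedes slow enrollment and contemplates a smaller target or collapsed groups. If the covariates are not fixed in advance, the gain is either lost or sought after the data are seen, when a choice of covariates is harder to defend.

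**Working it through.** **No stated figure to reproduce.** The article gives the target of 360 without alpha, power, entry rates or an effect size. Everything below is an illustration under assumptions.

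**Inputs from the article.** The target is 360, which is 120 per arm if allocation is equal. Enrollment was 28 (July 2021 to April 2023) plus 79 (May to July 2023), so 107, or 107/3 ≈ 36 per arm.

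**Assumed.** Entry of 20% versus 35% in a two-arm contrast, two-sided alpha 0.05, and one standardized baseline covariate.

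**Formula check at 120 per arm.** Power = Φ{[|p2 − p1| − 1.96·√(2p̄(1 − p̄)/n)] / √[(p1(1 − p1) + p2(1 − p2))/n]}, with p̄ = 0.275.
- Null standard error: √(0.39875/120) = 0.0576.
- Alternative standard error: √(0.3875/120) = 0.0568.
- (0.15 − 1.96 × 0.0576)/0.0568 ≈ 0.65, so power is 74.3%.

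If covariates explain a share R² of the outcome variance, replace n by n/(1 − R²):
- R² = 5%: n = 126.3, power 76.4%.
- R² = 10%: n = 133.3, power 78.6%.
- R² = 20%: n = 150, power 83.2%.

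At R² = 10% this is worth 360/0.9 − 360 = 40 participants over the whole trial.

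**Simulation.** Logistic regression with and without the covariate, 3,000 runs per setting:

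| Per arm | Covariate OR per SD | Unadjusted power | Adjusted power | Difference (points) |
|---|---|---|---|---|
| 120 | 1.0 | 74.5% | 74.3% | −0.2 |
| 120 | 1.5 | 75.1% | 75.7% | 0.6 |
| 120 | 2 | 74.4% | 77.5% | 3.1 |
| 120 | 3 | 75.3% | 81.7% | 6.4 |
| 36 | 1.0 | 30.4% | 29.5% | −0.9 |
| 36 | 1.5 | 28.5% | 28.6% | 0.1 |
| 36 | 2 | 29.3% | 30.2% | 0.9 |
| 36 | 3 | 29.0% | 32.2% | 3.2 |

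With equal entry of 27.5% in both arms, the rejection rate was 4.3% to 5.3% in every setting, with or without the covariate. The Monte Carlo standard error of one power figure near 75% is √(0.75 × 0.25/3000) ≈ 0.8 points. The two analyses in a row share data sets, so their difference is steadier than that, but differences below one point should be read as about zero. The R² approximation is somewhat more generous. The simulated figures are preferred because they come from fitting the logistic model itself.

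**Cost in parameters.** Condition and recruitment site take 2 + 2 = 4 effect parameters, and three single-term covariates bring this to 7. If overall entry were 20% to 35%, 107 participants would give about 21 to 37 events, or 3 to 5 per parameter. At 360 there would be 72 to 126 events, or 10 to 18 per parameter.

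**The case against.** The strongest reply is that nothing here is wrong. Leaving prognostic covariates out of a randomized comparison does not invalidate the test, and the simulated error rates bear this out. The list is worded as what the model will include, which does not close it, and a fuller analysis plan may name more. All of that stands. It limits the point to a suggestion about what the article names.

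The size can also be challenged, fairly. The covariates' prognostic strength is not given anywhere. Eligibility narrows their range, because everyone meets DSM-5 criteria for OUD, has used illicit opioids in the past 30 days and is not in medication treatment. Table 2 does not say what period or services treatment utilization covers. The simulation also compares against a model with no covariate, whereas the plan already adjusts for recruitment source, which may carry some of the same information. These points favor the lower end of the range.

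A reader might infer three stronger things that the documents do not support:

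- **That the mid-trial change in recruitment confounds the arms.** Allocation is concurrent in blocks of 3, 6 and 9, so a shift in who enrolls reaches all arms alike, and recruitment source is already in the model.
- **That a planned three-arm analysis of readiness cannot be done.** In the navigation arms "the Patient Navigator assesses readiness for SUD treatment, barriers to care, and other social determinants of health", and this happens after randomization. But the discussion under Progress to Date and Future Directions says that "it will be important to consider the association of social networks, such as familial support, on the primary outcome of treatment entry", so it commits only to considering social networks and support. Readiness appears there as a possible pathway. The assessment battery is described as open-ended, so absence from Table 2 does not prove that nothing is collected. Moving a navigator intake component to all arms would be a debatable change to usual care.
- **That the unadjusted result would be biased.** It would not be; the loss is in precision.

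**Conclusion.** The point holds as a minor efficiency improvement. The article names condition and recruitment source for the primary endpoint model and leaves three scheduled baseline measures unnamed. The stated analysis is valid. The forgone gain is about 1 to 6 power points at 120 per arm for a covariate odds ratio per SD of 1.5 to 3, and 0 to 3 points at about 36 per arm. Both ranges rest on assumed entry rates of 20% and 35%, two-sided alpha 0.05, a single covariate and a two-arm contrast. A covariate that predicts nothing costs a fraction of a point to about one point.

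**What to change.** Before outcomes are examined by arm, name a small set of baseline covariates for the primary treatment-entry model, in addition to condition and recruitment site. A workable order is baseline SUD treatment utilization and CIDI criterion count first. ASI-Lite opioid-use days would then be added under a rule, stated in advance, based on the total number of entry events pooled over arms. State the coding of each covariate and how missing baseline values are handled.

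Report the arm contrasts as standardized marginal risk differences from this model. The article names no effect measure, and an odds ratio adjusted for covariates is conditional on them. A standardized risk difference keeps a population-level meaning whichever covariates are included.

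The cost is a few sentences in the analysis plan, with no new data collection. The one downside is two or three extra parameters, which would be a strain if enrollment stayed near 107. The event-based rule is there to contain that.

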#### Hypothesis tests

For each outcome model, an omnibus test of the Condition factor will test whether the outcome differs across study arms. Single-degree-of-freedom contrasts will test the specific hypotheses that PN+BUP is superior to PN, which in turn is superior to UC. The contrasts correspond to the Condition effect for endpoint analyses (e.g., treatment entry; early remission of DSM-5 OUD) or the Condition X Time interaction for repeated measures analysis of differential change (e.g., Quality of Life).

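### Recruitment Site is listed only as a main effect in the repeated-measures models, so it gives little or no adjustment of the Condition x Time contrasts that are tested; a Site x Time term would.

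*Protocol article*

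**What the plan says.** Under Explanatory variables, the Protocol article puts Study Condition and "Recruitment Site (Clinic Site, Social Network, Other" into every model. The only further terms for repeated outcomes are given in one sentence: "For variables analyzed as repeated measures, the model will also include (3) *Time* and its interaction with *Condition". No Site x Time term is listed.

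Under Hypothesis tests, the single-degree-of-freedom contrasts are the Condition effect for endpoint outcomes and "Condition X Time interaction for repeated measures analysis of differential change (e.g., Quality of Life") for repeated ones. The same section also plans a broader test: "For each outcome model, an omnibus test of the Condition factor will test whether the outcome differs across study arms".

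Under Statistical Analysis, the model class is generalized linear models, "with extension to generalized linear mixed modeling for repeated measures models". Dichotomous outcomes are "assumed to follow a binomial distribution", counts are taken as Poisson, and alternatives are allowed where assumptions fail. Assessments are at baseline, 3 and 6 months. Randomization uses permuted blocks of 3, 6 and 9, and stratification by recruitment source is not mentioned.

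**The concern.** Recruitment source is the only covariate the article names besides Condition and Time, and the sample is mixed by source. Recruitment through the sexual health clinics yielded 28 participants up to April 2023. A further 79 enrolled from May to July 2023, after network referral opened. The Limitations section adds that paid referrals could bring in people without OUD, who might plausibly change differently on opioid-use outcomes.

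A reader would expect that listing Site protects the Aim 2 and Aim 3 change contrasts from an uneven spread of sources across arms. A term that is constant within a person cannot do that for a contrast built on within-person change. If clinic and network recruits follow different courses, a chance imbalance in source passes into Condition x Time, and the source-related variance in change stays in the error.

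**Working it through.** The article gives no alpha, power, effect size or event rates for these outcomes, so there is no planned figure to reproduce. The check is algebra, then simulation.

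**1. Algebra.** For participant i in arm c, from source s, at visit t, the listed model is

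g(E[Y_it | b_i]) = mu + alpha_c + sigma_s + tau_t + gamma_ct + b_i.

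- *Linear.* Change from baseline is (tau_t - tau_0) + (gamma_ct - gamma_c0) + error. Both sigma_s and b_i are gone. With complete visits, the Condition x Time estimate is the between-arm difference in mean change, whether or not Site is in the model.
- *Poisson.* Given a person's total count, the visit counts are multinomial with probabilities exp(tau_t + gamma_ct) / sum_u exp(tau_u + gamma_cu). Again sigma_s is absent.
- *Logistic.* The cancellation is exact only when conditioning on the person. The planned mixed model integrates over b_i, so it is approximate.

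**2. Simulation.** From the article: 360 participants (120 per arm under equal allocation) and three visits. Assumed: source mix 20/60/20%, Site effect scale 0.6, Site x Time scale 0 or 0.4, dropout 0% or about 25% related to source and arm, 20 to 25 data sets per setting. The figures are absolute shifts in the 6-month Condition x Time estimate, in SE units.

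| Step | Linear | Poisson | Logistic |
|---|---|---|---|
| Add Site main effect, complete visits | about 1e-13; SE ratio 1.0000 | about 1e-7; SE ratio 1.0000 | mean 0.005-0.006, max 0.017 |
| Add Site main effect, about 25% dropout | mean 0.06-0.07, max 0.22 | mean 0.07-0.09, max 0.29 | mean 0.04, max 0.08 (equal trajectories only) |
| Then add Site x Time, equal trajectories | mean 0.04-0.06; SE about +0.2% | mean 0.05-0.10 | mean 0.05-0.10; SE +0.6 to +1.1% |
| Then add Site x Time, differing trajectories | mean 0.18, max 0.61; SE about -1.5% | mean 0.21-0.32 | mean 0.05 (complete visits) |

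For the Condition coefficient itself (linear model, baseline as reference visit), the Site main effect moved the estimate by 0.23 to 0.38 SE and cut its SE by 5 to 11%. The term is therefore not idle in the model; it acts on level.

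**3. What could be at stake.** Take the clinic share as p = 28/(28 + 79) = 0.26. This is a proxy, since some of the 79 may not be network referrals and the final mix is unknown. Assume a within-source SD of change of 7.35 days and a difference in change between sources of d days. Neither figure is in the article.

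Share of change variance due to source = p(1-p)d² / [p(1-p)d² + 7.35²], with p(1-p) = 0.1924 and 7.35² = 54.02:

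- d = 3: 1.73/55.75 = 3%; SE reduction 1 - sqrt(1 - 0.031) = 1.6%
- d = 5: 4.81/58.83 = 8%; SE reduction 4.2%
- d = 8: 12.31/66.34 = 19%; SE reduction 9.8%

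The SD of the between-arm difference in clinic share is sqrt(2 x 0.26 x 0.74/120) = 5.7 percentage points. At d = 5, the SE of the contrast is sqrt(58.83 x 2/120) = 0.99 day. A one-SD imbalance shifts the contrast by 0.057 x 5 = 0.28 day, about 0.29 SE. A 10-point imbalance (about 1.8 SD) shifts it by 0.5 day, about half an SE.

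**4. Dropout.** If source affects both who is lost (differently by arm) and how people change, the source mix of those still observed differs between arms at follow-up. A model without Site x Time then carries that difference into Condition x Time as bias. In a separate linear mixed-model check under such dropout, adding the term removed most of the bias. The same check found no cost when trajectories did not differ by source, and a 5 to 12% lower sampling SD for assumed differences of 5 to 8 days.

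**The case against.** The strongest case against is that this is a modelling preference. A main effect for source is an ordinary, valid specification, and the article never says that Site is meant to adjust trajectories. Arms are randomized, so omitting Site x Time does not confound the contrast, and chance imbalance is already reflected in its standard error. The trajectory differences above are assumed, and in logistic models the added term raised the SE slightly. The article says that the variables will include those listed, so the full analysis plan may add more.

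Most of this stands and limits the point to a small one. It does not remove it: the article states which Time terms enter and which contrast is tested, and the two together give the named covariate almost no purchase on that contrast.

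Three stronger readings are tempting and should not be drawn.

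- *That Site does nothing for repeated outcomes.* It acts on the omnibus Condition test, it has a small effect when visits are missing, and the cancellation is only approximate in logistic models.
- *That Table 3 shows the enrolled groups to differ.* The 94.1% for network referrals against 2.4 to 10.1% for the clinic routes is past-30-day opioid use among people screened. The inclusion criteria require such use of everyone enrolled, so these rates show screening yield and say nothing about differences in course.
- *That the article itself identifies confounding of the change outcomes.* It does write "Still, there are potential confounders that may be introduced through the use of social network referrals", but that discussion concerns treatment entry, an endpoint outcome for which the main effect does adjust.

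**Conclusion.** The point holds as a low-severity one. As listed, Recruitment Site gives no adjustment of Condition x Time in linear and Poisson random-intercept models with complete visits, almost none in logistic models, and a small amount when visits are missing. The primary outcome and other endpoint models are unaffected.

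The cost is uncorrected chance imbalance and some lost precision, plus possible bias if dropout depends on source and arm and the sources change differently. The document does not show whether recruits from different sources change differently, so the size is unknown. Under the assumptions above it runs from nothing to a few tenths of an SE in the estimate on average, with up to roughly a tenth of the SE recoverable if sources differ by 8 days. It is probably small.

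**What to change.** Under Explanatory variables, add a fourth item for repeated-measures outcomes: *Recruitment Site x Time*. If baseline is instead handled as a covariate or constrained equal across arms, let the Recruitment Site effect differ between baseline and follow-up, which serves the same purpose. If the sponsor means Site to adjust overall level only, the text should say so. Either way, settle it before outcomes are examined by arm.

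The cost is 2 degrees of freedom with linear time (three source levels) or 4 with three categorical visits, against a target of 360 participants. The SE may rise negligibly if trajectories do not differ by source (about 0.2% in linear and 0.6 to 1.1% in logistic models in the simulations). No new data are needed, because source is already recorded and modelled.
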